### Outcomes {12}

The primary outcome of this trial is the ratio of COVID-19-related critical illness and all-cause mortality among the two groups within 28 days. COVID-19-related critical illness is defined as a patient who requires mechanical ventilation or extracorporeal membrane oxygenation or a patient maintaining oxygen saturation (SpO_2_) above 90% who requires high-flow oxygen inhalation with a fraction of inspired oxygen (FiO_2_) not less than 60% or requires noninvasive ventilation with a FiO_2_ not less than 60%.

The secondary outcomes are as follows: (1) COVID-19 viral load measured from pharyngeal swabs at the D1, D3, D7, and D14 timepoints, (2) incidence of azvudine-related adverse events (AEs) and serious adverse events, (3) duration of COVID-19-related symptoms, (4) all-cause mortality within 6 months, (5) days of hospitalization and intensive care unit stay, and (6) the ratio of COVID-19-related severe illness defined on the China Formula of Diagnosis and Treatment for COVID-19 (trial version 10). In detail are as follows: (1) shortness of breath with respiratory rate ≥ 30 breaths/min, (2) SpO_2_ ≤ 93% when inhaling air at rest, (3) partial pressure of arterial oxygen/FiO_2_ ≤ 300 mmHg, and (4) progressive worsening of clinical symptoms and obvious lesion progression > 50% on chest imaging within 24 to 48 h.

The safety endpoints consist of adverse events that emerge during or after the treatment period and subsequent observation period until 28 days. SAEs and AEs leading to discontinuation of the trial drug or placebo will be coded according to the definition of severe adverse events published by the FDA (https://www.fda.gov/safety/reporting-serious-problems-fda/what-serious-adverse-event).

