### Recruitment {15}

To account for a 10% dropout rate, the sample size increased to 1096 participants (548 in the azvudine group and 548 in the control group). To enrol enough participants, we set up special screening staffs in the fever clinic and emergency department where COVID-19 patients often visit, and screening staffs distribute COVID-19 antigen to suspected fever patients to identify candidates. In order to complete such large amount patients’ selection as soon as possible, we selected 46 study sites localized in 17 different provinces in China Mainland; thus, we will obtain timely enrolment to the greatest extent possible.

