## Data collection and management

### Plans for assessment and collection of outcomes {18a}

During the enrolment process, we plan to collect demographic information, including age, height, weight, blood pressure, heart rate, past medical history, smoking history, and laboratory parameters such as leukocytes, neutrophils, creatinine, uric acid, myocardial enzymes, pro-brain natriuretic peptide, hypersensitive C-reactive protein, D-dimer, and viral load upon admission (Table 3). These data are derived from the electronic medical record system of each participating hospital and will be documented on an electronic case report form (eCRF, https://study.cims-medtech.com/CIMS_V5/PlatFrame.aspx). Any AEs, including clinical symptoms and changes in vital signs, such as headache, dizziness, and nausea, and abnormalities observed in laboratory examination, including elevated serum creatinine AST or ALT, will also be documented. The correlation of AEs and the study drug or placebo will be carefully investigated. Furthermore, any changes in the patients’ conditions will be recorded during the follow-up period, which includes the 28th day after admission and up to 6 months.

Patients who are admitted to the hospital will be monitored on a daily basis until either a primary endpoint event occurs or they are discharged. A telephone follow-up will be conducted on the 28th day after admission to gather information about the patients’ survival status. For patients who remain hospitalized beyond 28 days, endpoint events will be recorded on the 30th day of their hospital stay.

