### Plans to promote participant retention and complete follow-up {18b}

Laboratory tests at the follow-up visit are all necessary to observe condition alterations or to ensure the safety of the patient. The current study showed that nucleic acid conversion was delayed compared to viral culture and was highest at 14 days, so we collected nucleic acid samples again at day 14 [22].

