## Statistical methods

### Statistical methods for primary and secondary outcomes {20a}

All data will be analysed using SAS software, version 9.4 (SAS Institute Inc., USA). A two-tailed *p* < 0.05 will be considered statistically significant in all statistical tests (except for the main efficacy indicators and other specified instructions).

The full analysis set (FAS), modified intention-to-treat set (mITT), per-protocol set (PPS), and safety set (SS) will be divided for analysis. FAS includes all eligible and randomized patients. PPS includes eligible patients with better compliance (80–120%), and completing necessary items of CRF.SS includes all patients enrolled in the study who have received at least one dose of medication and have at least one safety evaluation. Baseline characteristics analysis will be based on FAS, efficacy analysis will be based on FAS and PPS, and safety analysis will be based on SS. Unblinded patients will be excluded from PPS.

Continuous data will be summarized as the mean ± standard deviation, median, minimum, maximum, lower quartile, and upper quartile. Categorical data will be presented and summarized as frequencies and percentages in each category.

Between-group comparisons will be conducted by using paired *t*-tests or Wilcoxon rank tests for continuous data, chi-square tests or Fisher exact tests for categorical data, Wilcoxon rank tests or CMH tests for ranked data, and Kaplan‒Meier estimates for time-to-event data. The principles of intention-to-treat analysis will be used.

Efficacy analysis will be based on FAS and PPS. The primary efficacy endpoints are COVID-19-related critical illness and all-cause mortality within 28 days (whichever happens first), which will be analysed based on a time-to-event manner. Kaplan‒Meier method will be used to describe the incidence rates of the primary endpoint in each group separately at 28 days. Between-group comparisons will be performed by the log rank test. A Cox regression model will be used to estimate the hazard ratio and corresponding 95% confidence interval and adjust for potential covariates such as centres. Secondary efficacy endpoint analysis will be performed according to general statistical considerations. The specifics of these methods will be thoroughly outlined in the statistical analysis plan.

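### D1 viral load is listed as an outcome timepoint although it is the only available baseline, and the only methods named for the later visits are unadjusted two-group tests

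*Protocol article*

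**What the plan says.** Outcomes {12} defines secondary outcome (1) as "COVID-19 viral load measured from pharyngeal swabs at the D1, D3, D7, and D14 timepoints". It gives no metric, such as change from D1 or log10 copies, and does not mark D1 as different in kind from the other three visits.

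Two other places treat D1 as the entry value. Plans for assessment and collection of outcomes {18a} includes, among the data gathered during enrolment, "hypersensitive C-reactive protein, D-dimer, and viral load upon admission (Table 3"). Table 3 marks viral load at d1, d3, d7 and d14 and leaves the screening column empty, so no earlier sample exists.

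On analysis, Statistical methods {20a} states: "Between-group comparisons will be conducted by using paired *t*-tests or Wilcoxon rank tests for continuous data". For the secondary outcomes it adds: "Secondary efficacy endpoint analysis will be performed according to general statistical considerations". Covariate adjustment, with centre as the example, appears only for the Cox model of the primary endpoint. The paragraph closes with a deferral: "The specifics of these methods will be thoroughly outlined in the statistical analysis plan". That plan is not shown.

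**The concern.** One measurement has two roles that do not fit together. As an enrolment value, D1 describes the patients before treatment can act. As an outcome timepoint, it invites a test between the arms. If the swab precedes the first dose, randomisation makes the null hypothesis true at D1, so a significant result there can only be a chance finding.

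The same listing hides the use that D1 should have. Patients may enter at any time up to five days after symptom onset, so starting loads can be expected to differ. Some of that variation will carry over to D3 and D7. A two-group test that ignores D1 leaves it in the error term.

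The stake is modest but real. Viral load is the only virological outcome. On the protocol's own assumptions the primary endpoint will have few events: 493 × 0.026 + 493 × 0.0019 = 12.8 + 0.9, or about 14. If the primary result is null or fragile, readers will look to viral load to see whether the drug acted on the virus.

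**Working it through.** The protocol states no figure for viral load, so there is nothing of its own to reproduce. The check sets the passages against each other and then sizes the loss.

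**Role of D1.** Table 3 has no viral-load sample at screening, and {18a} collects viral load at enrolment. D1 is therefore the only candidate for a baseline. Outcomes {12} nevertheless lists it as an outcome visit. If the swab is pre-dose, a D1 test at two-sided 0.05 has a 5% chance of declaring a difference, and any such difference is false as evidence about the drug.

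**The named test.** A paired t-test needs matched observations. The arms consist of different patients randomised 1:1, so there are no pairs and the test named for between-group comparisons does not apply. The independent-samples t-test is presumably meant.

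**Inputs for the size of the loss.**
- Evaluable per arm: 548 randomised less 10% dropout (Recruitment {15}), 548 × 0.9 = 493.
- Two-sided α = 0.05 ({20a}), so z = 1.960.
- Power of 90% (z = 1.282) or 80% (z = 0.842), chosen for illustration.
- Correlation ρ between D1 and later log10 load: not given in the document. Assumed range 0.3 to 0.7.

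**Unadjusted comparison at one visit.** Detectable difference in SD units = (z for α + z for power) × √(2/n).
- 90% power: (1.960 + 1.282) × √(2/493) = 3.242 × 0.0637 = 0.206 SD.
- 80% power: (1.960 + 0.842) × 0.0637 = 0.178 SD.

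**Adjusted for D1.** The error variance is multiplied by 1 − ρ², so the detectable difference is multiplied by √(1 − ρ²). The power column takes the 0.178 SD effect that has 80% power unadjusted. The last column is the number per arm that gives the precision of 493 unadjusted.

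| Assumed ρ | Variance factor 1 − ρ² | Variance cut | Detectable at 90% power | Power for 0.178 SD | Equivalent n per arm |
|---|---|---|---|---|---|
| 0.3 | 0.91 | 9% | 0.197 SD | 84% | 449 |
| 0.5 | 0.75 | 25% | 0.179 SD | 90% | 370 |
| 0.7 | 0.51 | 49% | 0.147 SD | 97.5% | 252 |

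At a weaker ρ of 0.2 the cut is 4% and the detectable difference is 0.202 SD.

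**Simple change from D1 is not a substitute.** With equal SDs at the two visits, its variance relative to the unadjusted value is 2(1 − ρ): 1.4, 1.0 and 0.6 at ρ = 0.3, 0.5 and 0.7. It is worse than ignoring D1 when ρ is below 0.5. The covariate-adjusted factor is lower in each of the three cases.

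**The case against.** The strongest reply is that the protocol never says the arms will be tested at D1, or that D1 will be ignored later. Naming D1 among the sampling times commits nobody to either. The specifics are deferred to an analysis plan that is not shown, and baseline covariates for a secondary outcome are commonly set there. This stands as far as it goes: the unseen plan may already adjust. It does not remove the point. The outcome definition belongs to the protocol and lists D1 as an outcome. The method named here for continuous outcomes is unadjusted, and the word paired is an error in this document wherever the details are placed.

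A second reply is that the loss is of unknown size. This also stands. The correlation is assumed, and at ρ = 0.2 or 0.3 the gain is small.

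A reader might infer several stronger points that the documents do not support.
- *Local, unstandardised assays at 46 sites.* The protocol says "These data are derived from the electronic medical record system of each participating hospital", but that describes where the form entries come from, not who runs the assay. Site differences would in any case fall on both arms under randomisation, costing precision without causing bias.
- *A damaging visit window at D3.* With an assumed decline of 0.3 to 0.5 log10 per day, a window of one day either way adds an SD of about 0.24 to 0.41 log10. Against an assumed patient SD of 1.5 to 2.0 log10 that is only about 1.5% to 7% of variance.
- *An uninterpretable D14 mean.* The section on retention {18b} gives this reason for the D14 swab: "nucleic acid conversion was delayed compared to viral culture and was highest at 14 days, so we collected nucleic acid samples again at day 14". No proportion below the detection limit follows from this, and the rank test also named in {20a} treats such values as ties.
- *Restricting the analysis to patients with detectable RNA at D1.* This would depart from the FAS that {20a} sets for efficacy, with an unknown number lost.

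**Conclusion.** The point holds in a limited form. D1 is listed as an outcome although it is the only available baseline, and the methods named for the later visits leave it out. The protocol also names a paired test for independent arms.

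The cost is precision, not bias. Adjustment for D1 would cut the error variance by 9%, 25% or 49% at assumed correlations of 0.3, 0.5 or 0.7, and would raise the power for an effect at 80% to 84%, 90% or 97.5%. These figures assume 493 evaluable patients per arm and a roughly linear relation on the log10 scale. The statement about D1 assumes a pre-dose swab, which the document does not confirm.

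It would be wrong to read this as making viral load uninformative: unadjusted, a single visit still detects about 0.21 SD with 90% power. The change is worth making because the D1 value is already collected and using it costs almost nothing.

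**What to change.** In Outcomes {12}, label D1 as the baseline, state that the swab is taken before the first dose, and list only D3, D7 and D14 as outcome timepoints. State the metric as log10 viral load.

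In Statistical methods {20a}, replace the paired t-test with the independent-samples t-test for between-group comparisons. For viral load, name a comparison of the arms at D3, D7 and D14 in the FAS from a model with D1 log10 load as covariate. Centre may be added, as in the primary Cox model: at assumed site shares of variance of 0.05 to 0.30, this alone would lower the detectable difference from 0.206 to between 0.201 and 0.173 SD. Show D1 load by arm in the baseline table, without a test.

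The cost is wording in the protocol and agreement with the analysis plan, settled before unblinding. No new samples, visits or assays are needed. One detail needs a rule in the analysis plan: a patient without a D1 value would drop out of the adjusted model unless it says how that case is handled.

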### Eligibility criteria {10}

#### Inclusion criteria

Age of 18 years or older (inclusive)No more than 5 days since symptom onset and a positive result of nucleic acid and/or antigen test for COVID-19 within 5 days before enrolmentThe presence of at least one symptom related to COVID-19 infection at the time of enrolment (Table 1)

**Table 1 Tab1:** Subject’s symptom recording form

**Symptoms**	D1	D2	D3	D4	D5	D6	D7	……	D14	D28
Cough, sputum										
Sore throat										
Stuffy nose										
Running nose, sneezing										
Decreased sense of smell										
Decreased sense of taste										
Dyspnoea										
Headache										
Fever, chills										
Highest temperature of the day										
NSAIDs or not										
Muscle or joint pain										
Fatigue										
Nausea										
Vomiting										
Diarrhoea										

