### Strategies to improve adherence to interventions {11c}

The clinical research coordinator will determine if subjects are recording their condition daily by checking the subject’s symptom recording form (Table 1) and reminding each subject to take their medication daily. Upon completion of their medication, all subjects will be expected to return the medication package upon request.

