### Participant timeline {13}

After randomization, patients will receive the allocated interventions for 7 continuous days and be followed up for 6 months. The study schedule includes a screening visit; four treatment visits on day 1, 3, 7, and 14; and three follow-up visits on day 28, 3, months and 6 months. We will collect the patients’ survival status at follow-up visits. The participant timeline is shown in Table 3.

**Table 3 Tab3:** Schedule of screening, intervention and follow-up of the trial

Study periods	Screening	Treatment periods						Follow-up periods		
Time line		d1	d3 + / − 1	d4 to d6^a^	d7 + / − 1	d8 to d13^a^	d14 + / − 2	D28^a^ + / − 3	3 M^a^ + / − 7	6 M^a^ + / − 7
Consent form	X									
Check with inclusion and exclusion criteria	X									
Demographic characteristics	X									
Symptoms	X	X	X	X	X	X	X	X	X	X
Vital sign	X	X	X		X		X			
Adverse event		X	X	X	X	X	X			
Viral load		X	X		X		X			
Chest image (DXR or CT)		X			X		X	X		
Pregnancy test	X						X			
Blood routine	X	X	X		X		X			
Ferritin		X								
Interleukin-6		X								
Hypersensitive C-reactive protein		X	X		X		X			
Blood biochemical test	X	X	X		X		X			
Coagulation		X			X					
Oxygen level	X									
Cardiac troponin and N-terminal pro-brain natriuretic peptide		X			X					
Concomitant medication		X								

^a^Visits by phone calls

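### Symptoms are recorded about daily to day 14 and next at the day-28 call, so for patients at home who are still symptomatic at day 14 the end of symptoms is dated only to within days 14 to 28

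*Protocol article*

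**What the plan says.** Outcomes {12} in the protocol article lists "duration of COVID-19-related symptoms" as the third secondary outcome.

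Three places fix how symptoms are recorded:

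- Table 1, the "Subject’s symptom recording form", has columns D1 to D7, an ellipsis, D14 and D28. The ellipsis stands between D7 and D14; nothing stands between D14 and D28.
- Participant timeline {13} schedules "four treatment visits on day 1, 3, 7, and 14; and three follow-up visits on day 28, 3, months and 6 months". Table 3 marks symptoms at each of these. It also marks them in the telephone columns d4 to d6 and d8 to d13. Day 28 and the two later contacts carry the footnote "Visits by phone calls".
- Strategies to improve adherence {11c} relies on the same form: "The clinical research coordinator will determine if subjects are recording their condition daily by checking the subject’s symptom recording form". It gives no end day, and the form has no columns for days 15 to 27.

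Plans for assessment and collection of outcomes {18a} adds that admitted patients are monitored daily until a primary endpoint event or discharge, and that the day-28 telephone call gathers survival status. Statistical methods {20a} leaves the details of the secondary analyses to the statistical analysis plan, which is not at hand.

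**The concern.** A duration outcome is only as precise as the record of when symptoms stop. Here that record is close to daily for two weeks and then skips to day 28. The form lists cough, fatigue and loss of smell and taste, any of which may persist past day 14 in some patients.

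At stake is the precision of one of six secondary outcomes and, depending on how ends in the gap are scored, the size of the reported difference in days. The primary outcome, the safety analysis and the sample size are not touched. The point matters now because a date that is not collected cannot be recovered by any later analysis. The article describes recruitment as still under way, so for patients not yet past day 28 the date could still be obtained.

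**Working it through.** **1. The schedule.** The plan states no figure to reproduce, so the check starts from the two tables.

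| Days | Table 1 (diary) | Table 3 (symptoms row) |
|---|---|---|
| 1 to 14 | D1 to D7, ellipsis, D14 | d1, d3, d4 to d6, d7, d8 to d13, d14 |
| 15 to 27 | no column | no contact |
| 28 | D28 | D28 (telephone) |

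The two tables agree, so the gap is not an artefact of text extraction.

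**2. Width of the gap.**
- Days without a scheduled record: 27 - 15 + 1 = 13.
- With the windows (d14 ± 2, D28 ± 3), counting visits only: shortest 25 - 16 - 1 = 8 days, longest 31 - 12 - 1 = 18 days.
- A patient symptomatic at day 14 and well at day 28 has an end date somewhere in an interval 28 - 14 = 14 days wide. A midpoint of day 21 is wrong by at most 14 / 2 = 7 days.

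**3. Individual error if such an end were scored as day 28.** An end on day 15 gives 28 - 15 = 13 days too long; an end on day 27 gives 28 - 27 = 1 day. The error therefore runs from 1 to 13 days. If the date of a call held on day 31 were used, an end on day 15 would be 31 - 15 = 16 days too long.

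**4. Effect on a group comparison, under assumptions.** The article gives no symptom-duration figures, so everything in this step is assumed. True durations are log-normal with placebo median 8 to 14 days and log-SD 0.5 to 0.7. Azvudine shortens them by 15%, and values are capped at 28. The simulation used 400,000 patients per arm.

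Recorded value with day-28 scoring: the true day if 14 or less, otherwise 28.

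| Placebo median, log-SD | True difference (days) | Recorded difference (days) | Ratio | SD, true to recorded |
|---|---|---|---|---|
| 10, 0.5 | 1.63 | 2.33 | 2.33 / 1.63 = 1.43 | 5.5 to 8.6 |
| 14, 0.7 | 1.73 | 1.99 | 1.99 / 1.73 = 1.15 | 7.9 to 9.7 |

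Over the whole range of assumptions:
- About 12 to 41% of placebo patients end in the gap.
- Day-28 scoring overstates the mean difference by roughly 15 to 45% and inflates the SD by about 23 to 55%.
- Because the SD rises more than the difference, the standardised effect falls. In the first row, (2.33 / 8.6) / (1.63 / 5.5) = 0.271 / 0.296 = 0.91. In the second, (1.99 / 9.7) / (1.73 / 7.9) = 0.205 / 0.219 = 0.94.

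**5. The same model with other choices.**
- Gap ends scored at the day-21 midpoint: bias in the mean difference about -2 to +11% (about +10% at median 10, log-SD 0.5).
- Recorded median: unchanged at placebo medians of 8, 10 and 12 days; affected once the median reaches day 14.
- Wilcoxon test with 548 per arm, even with day-28 scoring: power 0.955 with true durations and 0.945 with recorded ones (median 10, log-SD 0.7).
- Duration cut off at day 14: no false dates, but the mean difference shrinks by about 23 to 60%.

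**The case against.** The strongest reply is that the gap is harmless until someone scores it badly, and the article contains no rule that does so. How to date an end that falls between two contacts is normal content of the statistical analysis plan, so its absence here is no fault. This stands. A reader might infer that everyone who recovers in the gap will be counted as day 28 and that the treatment difference will therefore be overstated. The article does not support that: day-28 scoring is an assumption, and under a midpoint, a median or a Wilcoxon test most of the distortion disappears.

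A reader might also infer that recovery on days 15 to 27 cannot be timed for anyone. That too goes beyond the text. Recovery is bracketed by two symptom contacts, and section {18a} has admitted patients monitored daily with no stop at day 14, so their recovery may be dated. That monitoring ends at discharge or a primary event, however, and does not help patients at home. Participants enter with mild-to-moderate disease, and screening staff work in fever clinics and emergency departments.

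Finally, the day-28 call might already ask when symptoms ended, since Table 3 marks symptoms there and a condensed article need not list every question. This is possible, but the text names only survival status as the purpose of the call.

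What the reply does not remove is the collection schedule itself. An analysis plan can handle an unknown date honestly, but it cannot supply the date.

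**Conclusion.** The point holds as a limit on precision. For patients not in hospital who are still symptomatic at day 14, the schedule dates the end of symptoms only to within days 14 to 28, or to day 31 with the visit window. Up to day 14 the dating is good to about a day.

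The effect on the outcome cannot be sized from the article, which states neither how many patients are affected nor how their durations will be scored. The range runs from a mean difference overstated by roughly 15 to 45% (day-28 scoring) to about -2 to +11% (midpoint), with no effect on a median below day 14. All of these figures rest on the assumed log-normal durations and the assumed 15% shortening. This is a cheap improvement to a secondary outcome, not a flaw that threatens the trial.

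**What to change.** 1. At the existing day-28 call, record for each symptom the calendar date on which it last occurred.
2. For patients still symptomatic at day 14, continue the self-completed Table 1 diary to D28 or until symptoms resolve, whichever comes first.
3. Treat any end that remains undated as lying in the interval day 14 to day 28, not as an exact day 28. This part belongs in the statistical analysis plan and may already be there.

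The cost is extra diary columns and one added item in a call that already takes place; no new visit is needed. The downsides are up to two more weeks of diary for those still symptomatic, and some recall error in dates given at day 28.
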